### Sample size

Preliminary data from a pilot study, which described global spectral EEG power-associated brain maturation in massaged preterm infants, was used to calculate a sample size [24]. To find a 10 % between-group difference in EEG power in the treatment group [24], with type 1 error rate 0.05, and power of 80 %, we require 20 participants in each group to complete the study. Assuming that two thirds of participants will remain in the study at term equivalent age, we will require a total of 60 preterm infants to be recruited (i.e. 30 per group).

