### Randomisation

Randomisation will be performed in Statistics Package for the Social Sciences (SPSS) 15.0 (SPSS Inc., Chicago, IL, USA) using random number generation with stratification by gender. The ratio of intervention to care as usual participants will be 1:1. A third party not involved with recruitment will generate the randomisation list and the list will be concealed. After random allocation lists have been generated, the allocation group (intervention or care as usual) of the premature infants will be stored in sequentially numbered, sealed, opaque envelopes. These envelopes will be opened by non-study personnel at each study enrolment, after baseline measures have been obtained.

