### Data analysis

Summary statistics will be used to describe demographic and clinical data characteristics at baseline by allocated study treatment. Continuous data will be summarised using either mean and standard deviation, or median and inter-quartile range, depending on the distribution of the variable of interest. Categorical data will be presented as frequencies and percentages. Comparisons between the baseline values of the treatment groups will be conducted to assess the degree to which variables are comparable after randomisation. Between group differences will be investigated using linear regression for continuous data and Fisher’s exact test for categorical data. Potential confounding variables for the primary outcome are considered a-priori to be: gestational age at birth, birthweight, parity and maternal education. If any of these variables differ significantly between-groups (at *P* < 0.005), the identified variable(s) will be controlled for in the main analyses.

The primary study outcome is beta frequency global power measured in all VPT infants at term equivalent age. The mean difference between treatment groups will be calculated using linear regression with treatment group entered as the main effect. The corresponding 95 % Wald confidence interval and *p*-value will be reported. For secondary outcomes, we will present the effect estimate relating to a variable with a continuous outcome as a mean difference, which will be calculated using a linear regression model. If a continuous variable does not meet the assumptions necessary for linear regression, we will compare groups using the Mann–Whitney U Test. We will present the effect estimate relating to a variable with a binary outcome as an odds ratio, which will be calculated using a logistic regression model. We will present the effect estimate relating to a variable with a count outcome as an incident rate ratio, which will be calculated using a Poisson regression model. For all models the corresponding 95 % Wald confidence interval and p-value will be reported.

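### Randomisation is stratified by gender, but the stated primary regression gives gender no route in, which costs precision if gender predicts beta power

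*Protocol article*

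**What the plan says.** The Randomisation section of the protocol article says that allocation is generated "using random number generation with stratification by gender". Gender is the only stratification factor named. The same section adds: "The ratio of intervention to care as usual participants will be 1:1". It does not mention blocks.

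The Data analysis section specifies the primary model: "The mean difference between treatment groups will be calculated using linear regression with treatment group entered as the main effect". The outcome is continuous: "The primary study outcome is beta frequency global power measured in all VPT infants at term equivalent age". A short covariate list comes before the model: "Potential confounding variables for the primary outcome are considered a-priori to be: gestational age at birth, birthweight, parity and maternal education". If any of these differs between groups at P < 0.005, "the identified variable(s) will be controlled for in the main analyses". Gender is in neither the model sentence nor the list.

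The Sample size section gives the design target, "To find a 10 % between-group difference in EEG power in the treatment group", with two-sided alpha 0.05 and 80% power, and concludes that "we require 20 participants in each group to complete the study". It assumes that two thirds of infants remain at term equivalent age and so recruits 60.

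**The concern.** A factor is normally chosen for stratification because it is thought to matter for the outcome, and the analysis should then carry it. Here the article fixes both the model and the candidate covariates, and gender cannot enter by either route, even if it turns out unbalanced among the infants who reach term equivalent age.

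If gender explains part of the variance of beta power, leaving it out puts that variance into the residual. The confidence interval is then wider than it need be, in a trial that expects only about 40 evaluable infants. If the allocation method also forces balance within gender, the unadjusted model takes no credit for that balance and its standard error overstates the true variability of the estimate.

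**Working it through.** **Inputs from the article.** 60 randomised 1:1 within gender; 20 completers per group; two-sided alpha 0.05; power 80%; 10% difference. **Assumptions.** The share of outcome variance explained by gender (R²) is not given, so 0 to 0.30 is shown. Blocking is not stated, so both possibilities are shown.

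**1. The plan's own figures.** The dropout step reproduces: 20 / (2/3) = 30 per group, 60 in total. The 20 per group cannot be reproduced because no SD is given, so the standardised effect was back-solved from it.
- Normal approximation: d = (1.960 + 0.842) × √(2/20) = 0.886, which implies an SD of 10/0.886 = 11.3%.
- Noncentral t, 38 df: d = 0.909, which implies an SD of 10/0.909 = 11.0%. This d is used below.

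**2. Analytic effect of omission, gender exactly balanced among completers.** The residual SD is σ without gender and σ√(1 − R²) with it, so the SE ratio is 1/√(1 − R²). Adjusted power uses the noncentral t with effect 0.909/√(1 − R²) and 37 df.

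| R² | SE ratio | Adjusted power (80% without gender by construction of d) |
|---|---|---|
| 0.05 | 1/√0.95 = 1.026 | 0.819 |
| 0.10 | 1/√0.90 = 1.054 | 0.839 |
| 0.20 | 1/√0.80 = 1.118 | 0.879 |
| 0.30 | 1/√0.70 = 1.195 | 0.917 |

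**3. Simulation with the planned dropout.** 60 infants were allocated within gender and 40 retained at random. The regression was fitted with and without gender to the same data sets, with 15,000 null and 6,000 alternative runs per row. The Monte Carlo error is √(0.05 × 0.95/15,000) = 0.0018 for type I error and √(0.8 × 0.2/6,000) = 0.005 for power. SEs are in outcome-SD units.

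Permuted blocks of 4 within gender:

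| R² | Unadjusted model SE v true SD | Type I error, without / with gender | Power, without → with gender |
|---|---|---|---|
| 0 | 0.3181 v 0.3168 | 0.0480 / 0.0483 | 0.794 → 0.791 |
| 0.05 | 0.3175 v 0.3126 | 0.0467 / 0.0490 | 0.799 → 0.815 |
| 0.10 | 0.3177 v 0.3093 | 0.0438 / 0.0505 | 0.796 → 0.823 |
| 0.20 | 0.3184 v 0.2936 | 0.0341 / 0.0461 | 0.810 → 0.878 |
| 0.30 | 0.3186 v 0.2822 | 0.0282 / 0.0485 | 0.811 → 0.912 |

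Unblocked random numbers within gender:

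| R² | Unadjusted model SE v true SD | Type I error, without / with gender | Power, without → with gender |
|---|---|---|---|
| 0 | 0.3203 v 0.3184 | 0.0471 / 0.0475 | 0.787 → 0.777 |
| 0.05 | 0.3204 v 0.3218 | 0.0536 / 0.0529 | 0.793 → 0.801 |
| 0.10 | 0.3204 v 0.3216 | 0.0511 / 0.0542 | 0.777 → 0.805 |
| 0.20 | 0.3205 v 0.3238 | 0.0557 / 0.0540 | 0.791 → 0.862 |
| 0.30 | 0.3209 v 0.3189 | 0.0497 / 0.0508 | 0.793 → 0.906 |

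**4. Reading the tables.**
- Power forgone by omitting gender is 1.6, 2.7 and 6.8 points (blocked) and 0.8, 2.8 and 7.1 points (unblocked) at R² 0.05, 0.10 and 0.20.
- The unadjusted SE exceeds the true SD only with blocking: 0.3177/0.3093 = 1.027 at R² 0.10 and 0.3186/0.2822 = 1.129 at R² 0.30.
- Without blocking, the SE is right and only precision is lost. The type I errors in that table scatter about 0.05 to a similar degree with and without gender.
- At R² = 0 adjustment gains nothing and costs 0.3 to 1.0 points, which is within or close to simulation noise.

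**The case against.** The best case for the plan is that an unadjusted regression is a valid primary analysis. Adjustment is then an efficiency gain rather than a repair, and its size depends on an R² that the article does not support at any value. That stands: if gender does not predict beta power, nothing is lost.

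A reader might infer that the standard error is simply wrong for this design and the test falls below its nominal 5%. That needs two things the article does not state: balance forced within gender, and a prognostic effect of gender. Under unblocked random numbers, which the Randomisation wording also fits, the unadjusted standard error is correct.

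A reader might also use larger departures from 5%. Fixing 10 boys and 10 girls per arm among completers gives a type I error of 0.038 at R² 0.10 and 0.028 at R² 0.20. The plan expects to lose a third of its infants, which disturbs that balance. With dropout the figures are 0.044 and 0.034.

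Finally, this is a condensed article, and its model sentence does not say that treatment is the only term. A fuller analysis plan may include gender. That limits the point but does not remove it, because the article does list the covariates it regards as relevant and gender is not among them.

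**Conclusion.** The mismatch between design and analysis is real: the one stratification factor has no route into the stated primary analysis. The consequence is conditional and moderate. If gender is prognostic, roughly 1 to 7 points of power are forgone at an assumed R² of 0.05 to 0.20, whether or not allocation is blocked. If allocation is also blocked within gender, the test is mildly conservative.

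The article does not support the inference that the trial is underpowered. Unadjusted power in the simulations is 0.78 to 0.81, near the planned 80%. That closeness is expected, because d was back-solved from the plan's own 20 per group, so it neither confirms nor refutes the sample size. Nor is there any bias or inflation of false positives, since any error in the standard error is on the cautious side. These results assume loss unrelated to gender or treatment and normally distributed residuals. The change is worth making because it costs almost nothing and brings the analysis into line with the randomisation.

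**What to change.** In the Data analysis section, state that the primary linear regression contains treatment group and gender as fixed terms, with gender included as the stratification factor regardless of observed imbalance and outside the P < 0.005 rule. Say the same for the linear models of continuous secondary outcomes.

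The change need not be extended to every secondary analysis. The Mann–Whitney fallback cannot take a covariate. In logistic models with about 40 infants, adding gender changes the odds ratio from marginal to conditional and can create sparse cells, so those models need a separate decision.

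The cost is one sentence and one residual degree of freedom (38 to 37), with no change to sample size or data collection. It should be fixed before outcome data are seen.

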### Secondary outcomes

i.Other EEG parameters at term equivalent age (TEA)Global power in delta, theta and alpha bands, absolute and relative power for each frequency band, interhemispheric coherence and partial directed coherence will be analysed.ii.MRI measures at TEAA brain MRI will be performed using a 3.0-T (Siemens TIM Trio, Erlangen, Germany) and an MRI-compatible incubator with a dedicated head coil (LMT Lammers Medical Technology, Lubeck, Germany). The infants will be fed, fitted with earmuffs to minimise noise exposure (Natus Mini Muffs, Natus Medical Inc., San Carlos, CA) and monitored by pulse oximetry, then wrapped and placed in an MRI-compatible incubator to keep the infant still, warm and supported in the scanner. Scanning will occur for about 45 to 60 min without sedation.The MRI protocol will include T1 turbo spin echo (TSE), T1w MPRage, T2w HASTE and 3 echo T2 map, 30 direction diffusion weighted imaging (DWI), and 64 direction DWI sequences. A neuroradiologist will review clinical sequences and classify any white and grey matter [58, 97] abnormalities. Diffusion images will be acquired using single-shot echo planar multi-direction diffusion-weighted sequence, employing dual bipolar diffusion gradient and double spin echo. This will include the acquisition of a 30 direction DWI protocol (b = 1000s/mm^2^) and a 64 direction HARDI protocol (b = 2000s /mm^2^), in which the encoding gradients are uniformly distributed in space (acquisition time 5 min and 11 min respectively). A field map for diffusion data is acquired using two 2D gradient recalled echo images to assist in correction for residual distortions due to susceptibility in homogeneities (acquisition time 1 min). An extensive pre-processing and quality control procedure will be used to detect and correct image artefacts caused by head movement, cardiac pulsation, and image distortions [60]. Fractional anisotropy (FA) and mean diffusivity (MD) will be estimated from corrected diffusion data using a diffusion tensor model. Constrained spherical deconvolution implemented in MRtrix will be employed to estimate fibre orientation distribution (FOD) [98]. Whole-brain voxel based analysis of FA and MD will be performed using tract-based spatial statistics optimised for neonates [99]. Whole-brain voxel-based analysis of fibre orientation distributions will be conducted using Apparent Fibre Density (AFD) [100]. Probabilistic tractography will be performed using MRtrix. White matter pathways will be delineated using the multi-regions-of-interest approach. A number of pathways, including corticospinal tract, corpus callosum, superior longitudinal fasciculus and thalamic radiations will be extracted. Summary measures of FA, MD, AFD and T2 within pathways will be calculated and related to EEG and clinical findings.iii.Preterm infant clinical measures8.Clinical assessments performed at baseline will also be performed at TEA; Prechtl’s Qualitative General Movements Assessment (GMA) [45] and Hammersmith Neonatal Neurological Examination (HNNE) [92]. All examinations will be performed by a Paediatric Neurologist, Paediatric Physiotherapist or Neonatologist blinded to allocation groups.A visual assessment will be performed at TEA. The Neonatal Vision Scale (NVS) [47] is a clinical assessment consisting of a short test battery that explores various aspects of visual function, ranging from the ability to fix and follow a target, to more complex aspects of visual function, such as reaction to a colour target, discrimination of black and white stripes with increasing spatial frequency and attention at a distance [47].The Bayley Scales of Infant and Toddler Development, Third Edition (Bayley-III) will be performed [48] at 24 months corrected age. Children will be assessed in the 5 key developmental domains of cognition, language, social-emotional, motor and adaptive behavior [48].The Infant Toddler Social and Emotional Assessment (ITSEA) will be measured at 24 months corrected age. The ITSEA is a 136-item parent report questionnaire to assess social and emotional problems and competencies in 4 domains of behavior: behavioural dysregulation; externalising behavior problems; internalising behavior problems and competencies [87].iv.Maternal measuresInfant Observation [85] performed at baseline will be repeated at TEA, 12 months and 24 months corrected age. This will be performed by the Psychoanalytic Psychotherapist who is blinded to randomisation.Questionnaires performed at baseline will also be performed at TEA; Depression Anxiety Stress Scales [79], Edinburgh Postnatal Depression Scale [95] and Mother-to-infant Bonding Assessment [96]. Mothers will be asked to complete these assessments.At 12 months corrected age, maternal infant responsiveness and maternal postnatal attachment will be measured. The MIRI, a 22-item scale [82] will be performed. The MPAS which has 19 items, all scored on a 5-point scale, with 1 and 5 indicating low and high attachment respectively, will also be performed [101]. Mothers will be asked to complete this assessment.At 24 months corrected age, the Maternal Self Efficacy Scale (MSES) will be measured. The MSES is a 20-item measure of the mothers’ perceived self-competence of their maternal practice used at 12 months. The measure has good internal consistency (Cronbach’s **α** = 0.76-0.89) and is a good predictor of maternal competence, with strong concurrent validity with observation [102]. Mothers will be asked to complete this assessment.

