All analyses will primarily be undertaken using the ‘intention-to-treat’ approach, where all evaluable data is analysed in the treatment group according to which the participant was allocated, regardless of treatment received. Additionally, ‘per protocol’ analyses will be conducted where there have been large deviations from the planned intervention; all individuals with evaluable outcome data will be analysed according to the treatment they received (no massage/received < 50 % of total possible massage/received at least 50 % of total possible massage). Any such analyses will be clearly labeled as such and cautiously interpreted as perhaps indicating the maximum theoretical potential of the intervention. Statistical significance will be defined as alpha = 0.05. All tests conducted will be two-tailed.

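### The Mann-Whitney fallback for continuous secondary outcomes gives a p-value without an effect estimate or interval, and forgoes adjustment for baseline scores the trial already collects

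*Protocol article*

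**What the plan says.** All of the following is in the protocol article.

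- **Default and fallback (Data analysis).** A continuous secondary outcome is reported as a mean difference from linear regression. The next sentence gives the exception: "If a continuous variable does not meet the assumptions necessary for linear regression, we will compare groups using the" Mann–Whitney U test. Binary and count outcomes get an odds ratio and a rate ratio. A 95% Wald interval and p-value are then attached to all models. No effect measure is named for the rank test.
- **Adjustment (Data analysis).** Four possible confounders are listed for the primary outcome: gestational age, birthweight, parity and maternal education. If one differs between groups at P < 0.005, "the identified variable(s) will be controlled for in the main analyses". No covariate is named for any secondary outcome.
- **Baseline data (Secondary outcomes, Table 1).** "Questionnaires performed at baseline will also be performed at TEA", meaning DASS, EPDS and MIBS. HNNE is also done at both times.
- **Stratification (Randomisation).** The list is generated "using random number generation with stratification by gender".
- **Size (Sample size).** "with type 1 error rate 0.05, and power of 80 %, we require 20 participants in each group to complete the study". This figure is for EEG power only; no secondary outcome has its own.

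**The concern.** The hypothesis on maternal depression, anxiety and stress rests on questionnaire totals. Each DASS scale has 14 items scored 0 to 3, so it is bounded at 0 and 42, and skewness is plausible. The document gives no distributions, so this cannot be confirmed.

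If such a score takes the fallback branch, the reader gets a p-value and nothing about size or precision. With about 20 completers per arm the interval is the most useful part of the result, because a non-significant p-value alone cannot separate no effect from an imprecise estimate. The same branch also leaves unused a baseline measurement of the same scale, which is the obvious candidate for a prognostic covariate.

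**Working it through.** **1. The plan's own figure.** The attrition step reproduces: 20 / (2/3) = 30 per group, 60 in total. The 20 itself cannot be reproduced outright, because no SD is given with "To find a 10 % between-group difference in EEG power in the treatment group". Back-solving at two-sided 0.05 ("All tests conducted will be two-tailed") and 80% power:

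- Normal approximation: d = (1.960 + 0.842) × √(2/20) = 0.886, an SD of 10/0.886 = 11.3.
- Noncentral t: d = 0.909, an SD of 10/0.909 = 11.0.

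The simulations below borrow d = 0.909 as a convenient scale. It is an assumption for the maternal and clinical scores, not a figure the document gives for them.

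**2. Fallback against the planned regression.** Neither analysis has a covariate. Simulated power, 20 per arm, 20,000 trials per scenario (r = 0, except that the lognormal and normal results are nearly the same at other r):

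| Assumed shape | Mann-Whitney | Unadjusted linear regression |
|---|---|---|
| Normal | 77–78% | 80% |
| Lognormal, sigma 0.5 | 78% | 75% |
| Lognormal, sigma 1 | 77–78% | 61% |
| Exponential, location shift | 94% | 80% |

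The rank test loses 2 to 3 points only on normal data, where the fallback would not be used. On skewed data it gains.

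**3. Fallback against a baseline-adjusted analysis.** First model: y = exp{0.6 × (√R² × z + √(1−R²) × e + 0.909 × group)}, where z is the baseline value, and z and e are standard normal. Regression of log y on group and z:

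| Assumed baseline R² | Adjusted log regression | Mann-Whitney | Gain |
|---|---|---|---|
| 0.1 | 82% | 77–79% | about 5 points |
| 0.2 | 86–88% | 77–79% | about 9 points |
| 0.3 | 91% | 77–79% | about 14 points |
| 0.5 | 97% | 77–79% | about 20 points |

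The ranges cover repeated runs. A further run of 20,000 trials per row gave 82, 87, 91 and 97% against 77 to 78%.

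Second method: rank ANCOVA with one covariate on lognormal data, against Mann-Whitney:

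- r = 0: 77% v 78%, a loss of about 1 point.
- r = 0.3 (R² = 0.09): 80–81% v 78%, a gain of 2 to 3 points.
- r = 0.5 (R² = 0.25): 86–87% v 77–78%, about 9 points.
- r = 0.7 (R² = 0.49): 95% v 77–78%, 17 to 18 points.

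On a bounded score that includes zeros, baseline-adjusted analyses reached about 79 to 95% for r = 0.3 to 0.7. Together these give the range of about 2 to 20 points.

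**4. Where the gain comes from.** In the first model with R² = 0, log regression has 80% power unadjusted and 79% with the covariate, against about 78% for Mann-Whitney. Nearly all of the gain is therefore the covariate and not the transformation. It is also available where the fallback is not used: on normal data, adjusted linear regression has 82, 89 and 97% at r = 0.3, 0.5 and 0.7, against about 80% unadjusted.

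**5. How often the adjustment rule triggers.** Four independent covariates at 0.005: 1 − 0.995⁴ = 0.0199, about 2% of trials by chance.

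**The case against.** Four objections deserve weight.

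- **Power.** A reader might infer that skewed outcomes lose power under the fallback. They do not, measured against what the plan would otherwise do: step 2 shows the reverse. The 2 to 20 points are against an analysis that the plan does not state. This stands, and the gain is an argument for an improvement, not evidence of an error.
- **The plan's own adjustment rule.** A reader might infer that the rank test makes this rule impossible to follow. The rule's covariates are listed for the primary outcome, while the fallback sentence sits in the text on secondary outcomes (although it speaks of continuous variables in general). A conflict arises only if the main analyses include secondary outcomes and a covariate also differs at P < 0.005. Adjustment for gender or baseline score is promised nowhere.
- **Contradiction.** The mean difference is tied to regression, the rank test is its stated exception, and the Wald interval is promised for models. The text does not strictly contradict itself. Nor is the method simply picked after seeing the data: both the alternative and its condition are written in advance, though the check itself is not described.
- **Detail left to the analysis plan.** An unseen analysis plan may name an effect measure for the rank test. That is possible. But the article does not leave the method open: it fixes a plain Mann-Whitney test, which cannot take covariates however it is reported.

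The simulations also favour log regression, since the first model is exactly lognormal. DASS totals can be zero, where a plain logarithm is undefined. The rank ANCOVA and bounded-score results do not depend on the logarithm and show the same pattern.

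**Conclusion.** The point holds in a limited form. For a continuous secondary outcome that fails the regression assumptions, the plan as written gives a p-value with no estimate or interval, and uses a test that cannot draw on baseline scores or gender. At 20 per arm, baseline adjustment would add about 2 to 20 points of power for an assumed baseline R-squared of about 0.1 to 0.5, and would cost about 1 point if the baseline were uninformative. These sizes rest on assumed distributions, an assumed baseline correlation, and an effect borrowed from the EEG calculation.

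The gain applies to DASS, EPDS, MIBS and HNNE. For outcomes with no baseline value (NVS, Bayley-III, MRI measures, MIRI, MPAS, ITSEA, MSES), only the missing estimate and interval matter. The primary conclusion is unaffected.

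**What to change.** In Data analysis, for secondary outcomes with a baseline measurement, make the main analysis a regression on treatment group, adjusted for the baseline score and gender. Where residuals are skewed, name one of these in advance: a transformation that allows zeros, such as log(y+1); robust or bootstrap intervals; or a rank ANCOVA. A rank ANCOVA gives no effect on the score's own scale, so report a shift estimate beside it.

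Wherever Mann-Whitney is still used, including outcomes with no baseline value, report a Hodges-Lehmann shift with a 95% interval. Add one sentence saying whether the P < 0.005 adjustment rule extends to secondary outcomes.

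No extra data are needed. The cost is wording and slightly more programming. Transformed effects must be back-transformed for reporting, and bootstrap intervals are only approximate at 20 per arm.

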### Potential confounders

Limitations include the single blinded nature of the study and the risk of potential contamination between intervention and CAU groups. Parents whose infants are allocated to the control group may be more likely to withdraw from the study after randomisation, if they perceive there is limited benefit to them.

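### The intention-to-treat analysis is a complete-case comparison with one third of infants expected to be lost, and no stated analysis tests whether those lost differ on the outcome

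*Protocol article*

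**What the plan says.** Four parts of the protocol article bear on this.

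- **Analysis set (Data analysis).** The main approach is labelled intention-to-treat and defined as one "where all evaluable data is analysed in the treatment group according to which the participant was allocated", whatever treatment was received.
- **Expected loss (Sample size).** The calculation states "we require 20 participants in each group to complete the study". Its allowance for loss reads "Assuming that two thirds of participants will remain in the study at term equivalent age", which raises the recruitment target to 60, or 30 per arm.
- **Who may be lost (Potential confounders).** "Parents whose infants are allocated to the control group may be more likely to withdraw from the study after randomisation", if they see limited benefit for themselves. No rate is given.
- **Model and additional analysis (Data analysis).** The primary model is a linear regression of beta global power on treatment group. Gestational age, birthweight, parity and maternal education are named in advance as potential confounders, but each enters only if it differs between groups at P < 0.005. The one additional analysis, called per protocol, regroups infants by massage received and is again confined to those with evaluable outcome data.

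Table 1 schedules the EEG in preterm infants at TEA only, with none at baseline or later.

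**The concern.** Because the EEG is taken once, an infant without a TEA recording contributes nothing to the primary regression. The set that the plan calls intention-to-treat is therefore the infants who completed the EEG, grouped by allocation. Within each arm, such a comparison estimates the effect in all randomised infants only if loss is unrelated to the outcome.

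The plan expects substantial loss and gives a reason why it may be unequal. Raising recruitment from 20 to 30 per arm restores power but does nothing about selection. If the control infants who leave have systematically different beta power from those who stay, the completer means can differ with no massage effect at all. The direction is unknown. None of the stated analyses would show how far the result depends on this.

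**Working it through.** **Inputs from the protocol**
- 20 completers and 30 recruited per arm; two thirds retained at TEA (Sample size).
- The calculation is made "with type 1 error rate 0.05, and power of 80"%, and the analysis section adds: "All tests conducted will be two-tailed".
- The target is a 10% "between-group difference in EEG power in the treatment group"; no SD is given.

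**Assumptions (not in the documents)**
- The gap in mean outcome between control infants who stay and those who leave: 0.25, 0.50 or 0.75 SD.
- Loss in the massage arm is unrelated to outcome.
- For the unequal-loss scenario: 6/30 = 20% lost in the massage arm and 14/30 = 47% in the control arm, which leaves 24 and 16, still 40 in total.

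**1. The plan's own figure.** 20 / (2/3) = 30 per arm, 60 in total. This reproduces. Expected loss is 60 × 1/3 = 20 infants.

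**2. Scale.** The 20 per arm cannot be rebuilt without an SD. Solving backwards with a two-sample t-test (n = 20 per arm, two-sided 0.05, 80% power) gives an implied standardised difference of 0.91 SD. That serves as the yardstick below.

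**3. Bias formula.** In one arm, let f be the fraction missing and g the mean of those observed minus the mean of those missing. The observed mean exceeds the mean of all randomised infants by f × g. The error in the massage-minus-control difference is f_M × g_M − f_C × g_C. If g = 0 in both arms, this is zero whatever f_M and f_C are. With g_M = 0, its size is f_C × |g_C|.

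**4. Numbers.** Type I error is the two-sided rejection probability from the noncentral t distribution with 38 degrees of freedom, noncentrality = bias / √(1/n_M + 1/n_C), and outcome SD of 1 among completers.

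| Loss, massage / control | Completers | Gap (SD) | Bias (SD) | Share of 0.91 SD | Type I error |
|---|---|---|---|---|---|
| 33% / 33% | 20 vs 20 | 0.25 | 0.333 × 0.25 = 0.08 | 9% | 5.8% |
| 33% / 33% | 20 vs 20 | 0.50 | 0.333 × 0.50 = 0.17 | 18% | 8.1% |
| 33% / 33% | 20 vs 20 | 0.75 | 0.333 × 0.75 = 0.25 | 27% | 12.0% |
| 20% / 47% | 24 vs 16 | 0.75 | 0.467 × 0.75 = 0.35 | 39% | 18.5% |

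The assumption about the massage arm matters. If both arms have a 0.50 SD gap in the same direction, the bias cancels at equal loss (0.333 × 0.50 − 0.333 × 0.50 = 0). At 20%/47% loss it is 0.467 × 0.50 − 0.20 × 0.50 = 0.13 SD.

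**5. Power.** With 40 completers, a 24:16 split gives 78.4% power against 80.0% at 20:20. Unequal loss costs little precision; the issue is bias.

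**6. Does the covariate rule help?** For a two-sided P below 0.005, the observed baseline difference must exceed t(0.9975) × √(2/n). At 30 per arm this is 2.918 × √(2/30) = 0.75 SD, and at 20 per arm 2.980 × √(2/20) = 0.94 SD. Smaller imbalances caused by loss leave the model unadjusted.

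**The case against.** The best defence has four parts.

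- **No contradiction.** A reader might infer that the plan assumes data missing completely at random and then contradicts itself by predicting selective control withdrawal. The documents do not support that. They state no missing-data assumption. The Potential confounders section says only that control parents may be more likely to leave, and gives no rate. It describes loss that depends on arm, and it does not say that the infants who leave differ in beta power. Loss that depends only on allocation leaves the comparison unbiased. This part stands.
- **The model is not strictly treatment-only.** Four baseline variables can enter. That is correct, but the threshold makes entry unlikely for the imbalances at issue, as step 6 shows.
- **An article may leave missing-data methods to a fuller document.** This holds for details such as an imputation model. It does not dispose of the point, because the article itself fixes the analysis set, the model, the covariate rule and the only additional analysis, and that analysis has the same restriction to evaluable data. The definition is given openly beside the label, so the label on its own is a minor matter.
- **Multiple imputation would be a poor primary analysis here.** There is no earlier EEG to impute from, and imputing by arm from seven or more predictors with about 20 completers per arm is fragile. It also cannot repair loss that depends on the unobserved EEG value. This stands, and the fix below reflects it.

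**Conclusion.** The point holds as a weakness in an analysis that the protocol has fixed. The primary comparison is a complete-case one on about 40 of 60 infants. It is open to bias if leavers and stayers differ on the outcome within an arm, and nothing stated in the plan examines that.

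Under the assumed control-arm gaps, bias at the planned loss runs from 0.08 to 0.25 SD and type I error from about 6 to 12%. The least favourable case shown, 47%/20% loss with a 0.75 SD gap, gives 0.35 SD and 18.5%. At the small end the effect is slight. Every gap, the random loss in the massage arm and the unequal split are assumptions, so these figures show sensitivity and do not forecast the trial's bias. The change is worth making because so much primary data is expected to be missing and the remedy is cheap.

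**What to change.** 1. Keep the comparison by allocation, but describe the set as randomised infants with a TEA EEG, and state the missing-data assumption on which it relies.
2. Adjust the primary model for a small prespecified set of baseline variables already collected, for example gestational age, birthweight and gender (the stratification factor), and drop the P < 0.005 trigger.
3. Add a delta-adjusted (tipping-point) sensitivity analysis: impute the missing TEA EEG values, shift them by arm over about −0.75 to +0.75 SD, and report where the conclusion changes. Multiple imputation belongs here and not in the primary analysis.
4. Report loss and its reasons by arm.

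The cost is a little more analysis work, with no extra infants or measurements. The downside is that at n = 60 the sensitivity results will depend on the imputation model and should be reported with that caution.
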